### Aim 2: To identify patient characteristics associated with the presence (versus the absence) of a PFO, and to use this "PFO propensity" to estimate the patient-specific probability that a PFO was pathogenically related to the index stroke. (Model #1)

Since PFOs discovered in patients with CS may be pathogenically related to the stroke or not, in Aim 2, we will use logistic regression models to identify patient characteristics that are associated with the presence of a PFO among patients with CS ("PFO propensity"). In previous work [7,11,21], we have shown that this "PFO propensity" can be related to the probability that a PFO is pathogenic (i.e. non-incidental) using Bayes' theorem and 2 simple assumptions: 1) if not for those strokes that are PFO-attributable, the probability of a PFO in a CS patient would be the same as in the general population (controls); and 2) the rate of PFO-attributable strokes in PFO-negative CS patients is near-zero. Under these conditions:

Since the patient-specific probability of PFO in CS is given by the PFO propensity (i.e. the prevalence of PFO in CS patients otherwise similar to the patient), the only additional term needed to estimate the probability that a PFO is incidental for a particular patient is the general rate of PFO in the population (PFO probability in controls).

To develop a predictive model for PFO propensity, we will explore crude associations (overall and within each database) between the presence of a PFO and clinical variables including the subject's age, gender, race, hypertension, diabetes, hyperlipidemia, history of prior episodes of cerebral ischemia, obesity, antithrombotic medications, concurrent deep venous thrombosis, and neuroradiologic variables (i.e. prior stroke on MRI or CT, small [< 1.5 cm] versus large infarct, location of infarct). Multivariable associations between predictors and the presence of a PFO will be examined using logistic regression models. Selection of candidate variables for these models will be based on clinical rationale and the published literature. Variables with statistically marginal associations in the preliminary analyses (p > 0.15) will be removed. Non-linear associations between independent risk variables and the outcome will be investigated using generalized additive spline models[22]. As indicated, appropriate parametric logistic regression models will be developed to capture these non-linear relationships.

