Statistical significance of individual variables in the final model will be assessed with the Score statistic. Based on clinical reasoning, a limited number of interaction terms between risk factors may also be tested for inclusion in the model. The models will be analyzed by conventional criteria, such as goodness-of-fit tests, and receiver operator characteristics (ROC) curve areas [23]. "Calibration" of predicted probabilities of outcome throughout the range of their predictions will be evaluated with plots. The final multivariable regression models will be run separately on each of the component datasets to assess the consistency of the results and model performance. Based on these results, interaction terms between indicator variables representing study and model predictors of PFO will be used to investigate significant variation in associations across study datasets. Predictors found to be inconsistent across studies may be removed from the model. We will reanalyze the data using a generalized linear mixed model that includes a random effect term for study to get final parameter estimates with their corresponding standard errors.

Adequacy of the Data for Aim 2: Based on a preliminary review of the included studies (see Table 1), we will have potentially 3,101 subjects available for the models predicting PFO (1,332 with and 1,769 without PFOs), drawn only from those databases enrolling all cryptogenic stroke patients with and without PFO. This sample size will provide 80% power to detect an odds ratio of 1.23 for a balanced risk factor. For a risk factor with a prevalence of 20%, this sample size will still provide 80% power to detect an odds ratio of 1.29. The study will still provide sufficient power to detect clinically relevant associations even in the presence of significant data being unavailable for modeling. For example, if we totally eliminate data from the largest RoPE component study (the German database [24]), we will have 1,975 included subjects (928 with and 1047 without PFOs.) This sample will provide 80% power to detect odds ratios of 1.29 and 1.38 for risk factors with a prevalence of 0.50 and 0.20, respectively. Since outcome data is not needed for this analysis, loss of this amount of data is unlikely and the database would anyway still have ample power, permitting full exploration of multiple variables.

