### Aim 3. To develop a predictive model to estimate patient-specific recurrence risk based on clinical, radiographic and echocardiographic characteristics in patients with PFO and CS. (Model #2)

For Aim 3 we will use Cox proportional hazard models to develop a predictive model to estimate patient-specific recurrence risk. Because patients with CS with higher PFO-related recurrence risk generally have a lower prevalence of conventional stroke risk factors[25], failure to adjust for general (non-PFO-related) recurrent risk can lead to paradoxical results. This has been a major challenge for prior studies, since the low rate of outcomes limits the statistical power to control for conventional stroke risk factors and model PFO-related risk. While in the RoPE study we will have many-fold the number of outcomes compared to any prior study, statistical power for this analysis remains an issue.

To address this, depending in part on the number of outcomes, we will consider a two-step approach, that takes advantage of the outcomes in the component of the RoPE database of CS patients *without *PFO. First, we will construct a model for recurrence risk on the component of the study of CS patients *without *PFO. Next, we will construct a model for recurrence risk on the component of the study of CS patients *with *PFO, using the derived risk variable from the first step to control for the confounding background risk of stroke from PFO-unrelated causes. This will permit background stroke risk to be controlled for in a statistically efficient fashion. For step two, using the study subjects with known PFO, we will pay particular attention to echocardiographic information (e.g. hypermobility of the interatrial septum, interatrial shunting at rest, severity of interatrial shunt, anatomical PFO size, presence/absence of spontaneous flow on color Doppler)--to identify features of "high-risk" PFOs.

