Preliminary analyses for both phases of this two step process (i.e. modeling recurrence risk in patients without PFO and modeling recurrence risk in patients with PFO) will investigate associations between established risk factors and recurrent strokes. Kaplan-Meier survival curves and logrank tests will be used to assess statistical significance. For each phase, a multivariable prediction model for recurrent stroke will be developed using a Cox proportional hazard model, using an approach otherwise similar to that described for Aim 2. Predictive discrimination will be assessed using the overall C index [26]. Model calibration is assessed by comparing predicted survival probabilities against Kaplan-Meier (observed) probabilities across equal-sized risk quantiles (based on predicted recurrence probabilities). Differences between predicted and observed probabilities will be compared using a modified Hosmer-Lemeshow χ^2 ^statistic [27]. The Cox models be re-run including the study as a stratification factor to control for potential between-study differences in baseline survival functions when estimating hazard ratios of potential risk factors.

Adequacy of the data for Aim 3: Power was calculated on extreme optimistic and extreme pessimistic calculations. To obtain outcome rates for our sample we used databases with patients who had PFOs. We optimistically estimate available follow-up data for up to 1,752 patients with PFO; 1,332 from databases with both PFO and non-PFO patients and an additional 420 from databases that only have data on patients with PFOs. Based on the average outcome rates on the observed data, the estimated stroke rate for these patients is 6%. The sample size of 1,752 will provide 80% power to detect a clinically relevant hazard ratio of 1.77 for a risk factor with a prevalence of 50% and an overall stroke rate of 6%. Most pessimistically, we excluded 100% of our largest study (the German study [24]) and estimated follow-up will only be available for 70% of the remaining subjects which would result in a total sample size of 944. With this extremely conservative estimate of the sample size the study will have 80% power to detect a hazard ratio of 2.22 assuming an overall stroke rate of 6% and a risk factor prevalence of 50%.

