While having a sample size toward this lower estimate would still be adequate to detect these moderate to large effects, it would require us to be parsimonious in testing variables to avoid over-fitting (only about 60 stroke outcomes in PFO patients). After final database construction, we will consider whether to model the risk of the composite outcome stroke and transient ischemic attack (TIA). This has an outcome rate of 11.2% on the sample of our database with completed follow-up, virtually doubling the number of outcomes.

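### Model #2 is to be selected with a p > 0.15 screen on about 57 to 105 strokes, and the composite index is fixed before any check on patients outside the development data

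*Protocol article*

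**What the plan says.** Under Aim 2, candidates are first chosen on clinical rationale and literature. Then "Variables with statistically marginal associations in the preliminary analyses (p > 0.15) will be removed". Non-linear terms and a few interactions may be explored. The final models "will be run separately on each of the component datasets to assess the consistency of the results and model performance", and predictors that look inconsistent across studies may be dropped.

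Under Aim 3, "we will use Cox proportional hazard models to develop a predictive model to estimate patient-specific recurrence risk", with each phase built "using an approach otherwise similar to that described for Aim 2". The measures named are an overall C index, predicted against Kaplan-Meier probabilities by risk quantile, and a modified Hosmer-Lemeshow statistic. The Cox models are then re-run stratified by study.

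The article sees that events are scarce. At its lower sample size it expects "only about 60 stroke outcomes in PFO patients" and says that this calls for parsimony. It will consider a two-step approach that condenses background risk into one derived variable, and a combined stroke/TIA outcome.

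Aim 4 requires the stratification to be fully specified before trial outcomes are examined. Aim 5 then tests the index as a continuous variable and validates Model #2 on the pooled medical arms.

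**The concern.** A univariable p-value screen on few events keeps some noise variables and favours real ones whose effects happen to be overestimated. A Cox fit on the survivors then gives predictions that are too spread out, and a C index computed on the same patients looks better than it will elsewhere. Quantile calibration on the development data will not reliably show the problem either.

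This matters here because of the order of the steps. Model #2 is combined with the Model #1 probability to give the PFO-attributable recurrence risk, and that index is fixed before Aim 5. Noise variables re-rank patients. Excess spread in Model #2 gives it too much weight relative to Model #1. The one check on new patients comes after the point at which either fault could be corrected.

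**Working it through.** **1. Events, and the article's own power figures.** Inputs from Aim 3: N = 1,752 or 944 patients with PFO, stroke rate 6%, risk-factor prevalence 50%.
- Events: 0.06 × 1,752 = 105.1; 0.06 × 944 = 56.6 (the article says about 60).
- The 944 can be rebuilt. Aim 2 has 1,332 patients with PFO, or 928 without the German study, a difference of 404. Then (1,752 − 404) × 0.7 = 943.6.
- Power, Freedman form, two-sided alpha 0.05 assumed: Φ(√events × (HR − 1)/(HR + 1) − 1.96).
  - HR 1.77: Φ(10.25 × 0.278 − 1.96) = 81.3%.
  - HR 2.22: Φ(7.53 × 0.379 − 1.96) = 81.4%.

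Both agree with the stated 80%, so the event counts are those the plan itself relies on.

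**2. Events per candidate.** Table 2 has 17 clinical, 5 echocardiographic and 3 radiological rows, 25 in all.

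| Candidates | Strokes, N = 1,752 | Strokes, N = 944 | Stroke/TIA (11.2%), N = 1,752 | Stroke/TIA, N = 944 |
|---|---|---|---|---|
| 25 | 4.2 | 2.3 | 7.8 | 4.2 |
| 10 | 10.5 | 5.7 | 19.6 | 10.6 |
| 6 | 17.5 | 9.4 | 32.7 | 17.6 |

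**3. Expected shrinkage without selection.** S = LR/(LR + P), where P is the number of parameters and LR is the model's true likelihood-ratio information. LR is taken from an assumed Nagelkerke R² of 0.05 to 0.15. Example: N = 1,752, R² 0.05, LR = 32.3, P = 25 gives 32.3/57.3 = 0.56.
- P = 25: 0.56–0.80 (N = 1,752); 0.41–0.68 (N = 944).
- P = 10: 0.76–0.91; 0.63–0.84.
- P = 6: 0.84–0.94; 0.74–0.90.

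At R² 0.15, reaching S = 0.9 needs about 239 events for 25 parameters or about 96 for 10.

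**4. Simulation with the screen.** Univariable Cox screen at p ≤ 0.15, then an ordinary Cox fit, tested on independent patients. The first five rows use independent binary candidates of 30% prevalence and about 150 development sets. The last row uses effects of HR 1.28 per SD with 25 to 40 sets, 3 to 5 of the 6 candidates real, and the background score treated as known.

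| Setting | N | Apparent C | C in new patients | Calibration slope |
|---|---|---|---|---|
| 25 candidates, 6 real at HR 1.5 | 1,752 | 0.66 | 0.60 | 0.59 |
| same | 944 | 0.69 | 0.57 | 0.38 |
| 25 candidates, 6 real at HR 1.77 | 1,752 | 0.71 | 0.66 | 0.74 |
| same | 944 | 0.72 | 0.63 | 0.55 |
| 25 candidates, none real | 1,752 / 944 | 0.59 / 0.635 | 0.50 | about 0 |
| 6 candidates | 1,752 / 944 | gap about 0.025 / 0.04–0.05 | | 0.83–0.84 / 0.68–0.75 |

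With 25 candidates and six real ones, about three noise variables survive the screen on average.

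**5. Per-database refits, if applied to Model #2.** At 6%, APRIS (17 with PFO) gives 17 × 0.06 = 1.0 event, NOMASS 23 × 0.06 = 1.4, and the German study 389 × 0.06 = 23.3.

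**6. External check.** With 700 patients per arm and a 5% rate (Aim 5), the medical arms hold about 700 × 0.05 = 35 events.

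**The case against.** The article has more safeguards than the word parsimony. Candidates are first chosen on clinical grounds, final variables are agreed by investigator consensus, the two-step approach would shrink the PFO-stage model to a background score plus a handful of echocardiographic features, and stroke/TIA would nearly double the events. Table 2 is provisional and serves both models, so 25 is an upper bound and not a committed model. All of this stands, and it is why the size must be given as a range. But no numeric cap is stated, the two-step approach and the wider outcome are only to be considered, and six candidates still leave slopes below 1.

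A reader might infer that the fit is unpenalised and that no optimism correction will be made. The article does not say so. It names Cox models and is silent on shrinkage and resampling, which a fuller plan may cover. The point rests on what is stated: the screen, its carry-over, the event counts and the order of the steps.

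A reader might also take the per-database refits as planned for Model #2. They are written for Model #1. Aim 3's own between-study step is stratification, and the refits reach Aim 3 only through the phrase about a similar approach.

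Finally, external validation is planned, with ROC areas and calibration plots as well as goodness-of-fit tests. That stands too, so performance is not judged on development data alone. Its limits are its timing and about 35 events.

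**Conclusion.** The concern holds as an avoidable weakness in how Model #2 is selected and checked. With the stated screen and 57 to 105 strokes, the calibration slope in new patients would be about 0.4 to 0.75 if all 25 listed variables were screened, and about 0.7 to 0.85 with about six under the two-step approach. These figures assume independent predictors, the effect sizes shown, an ordinary Cox fit and, for six candidates, a background score known without error. The event range is itself approximate: Table 1 sums to 1,286 patients with PFO in mixed databases and 662 in PFO-only ones, against 1,332 and 420 in Aim 3.

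Over-fitting is a likely risk and not a certainty. With ten parameters and 105 events, expected shrinkage before any selection is 0.76 to 0.91.

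It is tempting to conclude that an over-fitted index would produce a false-positive interaction in Aim 5. The documents do not support that: the index is fixed before trial outcomes are seen, so its noise is unrelated to them. What is lost is power and calibration. Uniform excess spread would leave ranks within Model #2 unchanged. Noise variables, and the combination with Model #1, would alter the composite ranking.

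**What to change.** For Model #2:

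- Replace the p > 0.15 screen with a candidate list fixed in advance on clinical grounds and capped at a number the observed events support, for example the two-step background score plus the echocardiographic features.
- Fit it with shrinkage or penalisation.
- Before the composite index is frozen, report bootstrap optimism-corrected C index and calibration slope, repeating every modelling step in each resample.
- Do not remove Model #2 predictors on the basis of per-database refits. Use leave-one-database-out checks across the larger databases.
- In the trial medical arms, report a censoring-aware C index and calibration slope with confidence intervals alongside the planned plots.

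The cost is analysis time, with no new patients or data. Reported performance will look less favourable, and shrunken coefficients are harder to present singly.

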### Aim 5: To apply this score to patients in completed clinical trials (currently on-going) testing percutaneous PFO closure against medical therapy, from low-expected-benefit to high-expected-benefit

The primary hypothesis of Aim 5 is that there will be a treatment-by-index interaction, when patients enrolled in RCTs testing PFO closure are ranked by their risk of stroke recurrence, conditioned on the probability that the PFO was pathogenically-related to the index event (using the composite index as a continuous variable). A p-value of 0.05 will be the threshold for significance. Depending on results, a clinically usable model will be developed. This step comprises external validation of the combined model. In addition, model 2 (the CS recurrence risk model) will be externally validated on the pooled medical arms of the RCTs by conventional criteria, including goodness-of-fit tests, ROC curve areas and calibration plots as described in the prior aims.

For Aim 5, we have, as of this writing, received agreement to test the risk models on two RCT databases, which will be pooled. Additional RCTs will be sought. The two RCTs to be pooled are:

Randomized Evaluation of Recurrent Stroke comparing PFO Closure to Established Current Standard of Care Treatment (RESPECT) Trial: (http://ClinicalTrials.gov identifier: NCT00465270) This is a prospective, randomized, multi-center trial, enrolling at 60 North American centers, designed to investigate whether percutaneous PFO closure with the Amplatzer PFO Occluder is superior to current standard of care medical treatment in the prevention of recurrent stroke. Inclusion criteria include age of 18-60 years old, cryptogenic stroke (not TIA) within 270 days, and TEE demonstration of a PFO. The recruitment target is 1000 subjects who will be randomized 1:1 to endovascular PFO closure or medical management. The primary endpoints are recurrence of non-fatal stroke, post-randomization death, and fatal ischemic stroke.

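### Model #1 (PFO propensity) is assessed only on the databases that built it, and the PFO-only trials of Aim 5 cannot supply an out-of-sample check

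*Protocol article*

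**What the plan says.** Aim 2 sets the general criteria for Model #1: "The models will be analyzed by conventional criteria, such as goodness-of-fit tests, and receiver operator characteristics (ROC) curve areas", together with calibration plots. It names no held-out data. The per-database step follows: "The final multivariable regression models will be run separately on each of the component datasets to assess the consistency of the results and model performance". Depending on what that shows, "interaction terms between indicator variables representing study and model predictors of PFO will be used to investigate significant variation in associations across study datasets", and "Predictors found to be inconsistent across studies may be removed from the model". The last step re-estimates the model on all the data, using a "generalized linear mixed model that includes a random effect term for study to get final parameter estimates".

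Aim 5 names external validation twice. Of the treatment-by-index interaction test in the randomised trials it says: "This step comprises external validation of the combined model". It adds that "model 2 (the CS recurrence risk model) will be externally validated on the pooled medical arms of the RCTs", with goodness of fit, ROC area and calibration plots. Model #1 has no matching sentence. RESPECT requires a PFO shown on TEE. The PC-Trial is described as a closure trial of very similar design, so its patients also have a PFO (inferred from that description).

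Aim 4 converts the propensity into a probability that the PFO is pathogenic, using a control PFO rate (Figure 1 shows 15%, 20% and 25%). It combines that probability with Model #2 and fixes the stratification before trial outcomes are examined.

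**The concern.** The propensity will be applied to patients from populations that did not contribute to it. The question is therefore whether a propensity built in some databases predicts PFO correctly in another. The stated check does not answer this. If the model is re-fitted in each database, the resulting ROC area describes a new model on its own data. If the pooled coefficients are applied, they were estimated partly from that same database. The per-database results may also change the predictor set, which makes them part of model development.

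Aim 5 cannot close the gap. With no PFO-negative patients, presence versus absence of PFO is not an outcome there. The interaction test uses the composite index, so a null or positive result cannot be traced to the calibration of Model #1. If the propensity is off in a new population, the attributable probability is off with it, and the frozen index carries the error forward unseen.

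**Working it through.** **1. The plan's own figures.** Table 1 has eight databases with and without PFO: 83 + 486 + 581 + 1,126 + 172 + 60 + 250 + 343 = 3,101, the Aim 2 sample size. With 1,332/3,101 = 0.430 PFO-positive, 80% power and two-sided 5% significance (assumed; Aim 2 states none), the detectable odds ratio is exp[(1.96 + 0.84)/√(3,101 × 0.430 × 0.570 × q(1 − q))]. This gives 1.23 at risk-factor prevalence q = 0.5 and 1.29 at q = 0.2, as stated. The sample inputs are sound; the point concerns validation, not power.

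**2. Where each performance check of Model #1 takes its data.**

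| Check | Data | Out of sample? |
|---|---|---|
| Goodness of fit, ROC area, calibration plots | no held-out data named | none described |
| Per-database run | component databases | no |
| Study-by-predictor interactions | component databases | no |
| Mixed model with random study effect | component databases | no |
| Treatment-by-index interaction | randomised trials | yes, but for the composite index |
| ROC area and calibration in medical arms | randomised trials | yes, but for Model #2 |

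**3. Spread between databases.** Raw PFO share is 17/83 = 20.5% in APRIS and 93/172 = 54.1% in Lausanne; the German database has 389/1,126 = 34.5%. Over the eight databases, chi-square is 80.9 on 7 df and I-squared is 91%. CODICIA's row does not add up (266 + 240 = 506, against 486 stated). The figures above use 506, a share of 52.6%; 266/486 would give 54.7% and 246/486 would give 50.6%, so the picture does not change. None of this is adjusted for case mix.

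**4. Sensitivity of the attributable probability.** Let p be the propensity and c the control rate. Under Aim 2's two assumptions, PFO-negative patients (share 1 − p) all have non-attributable strokes, so incidental PFOs make up c(1 − p)/(1 − c) of patients. Hence

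attributable probability = 1 − c(1 − p)/[(1 − c)p], with slope [c/(1 − c)]/p².

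Effect of a 3-point error (0.03 × slope):

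| c | c/(1 − c) | at p = 0.25 | at p = 0.50 |
|---|---|---|---|
| 15% | 0.176 | 0.03 × 2.82 = 8.5 points | 0.03 × 0.71 = 2.1 points |
| 20% | 0.250 | 0.03 × 4.00 = 12 points | 0.03 × 1.00 = 3 points |
| 25% | 0.333 | 0.03 × 5.33 = 16 points | 0.03 × 1.33 = 4 points |

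These are slope values. At c = 25% and p = 0.25 the attributable probability is exactly 0, so only an upward error counts. Moving to p = 0.28 gives 1 − 0.333 × 0.72/0.28 = 0.143, or 14.3 points.

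**5. Why the absolute level matters for ranking.** At c = 20%, patients with p = 0.25 and p = 0.50 have attributable probabilities 0.25 and 0.75, a ratio of 3.0. Raise both propensities by 3 points: 1 − 0.25 × 0.72/0.28 = 0.357 and 1 − 0.25 × 0.47/0.53 = 0.778, a ratio of 2.2. If the index were a product with recurrence risk (an assumption; the article leaves the combination open), two such patients would change places whenever the first had between 2.2 and 3.0 times the second's recurrence risk.

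**6. Feasibility of a held-out check.** Training sets run from 3,101 − 1,126 = 1,975 to 3,101 − 60 = 3,041. At an assumed ROC area of 0.70, the 95% half-width in the held-out database is about 0.03 (German), 0.04 (PFO-ASA), 0.05 (CODICIA), 0.06 (Sapienza), 0.07 (PICSS), 0.08 (Lausanne), 0.14 (NOMASS) and 0.15 (APRIS).

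**7. Direction only.** In a simulation with assumed inputs (20 predictors, 6 of them real; CODICIA, German, Lausanne and Sapienza held out in turn), the mean ROC area was about 0.73 re-fitted per database and 0.68 held out. The mean absolute error in calibration-in-the-large was about 0.02 with a common baseline. It was about 0.09 when the Table 1 shares were taken as baseline differences that no predictor explains.

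**The case against.** **The article is condensed.** Bootstrap or cross-validation may stand in a fuller plan, and their absence here is no error. That stands. But the article does commit to a specific performance check, and that check cannot show performance in an unseen database. It also states external validation for Model #2 and the composite index.

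**Re-fitting is not stated.** True. It is the likelier reading, because the results are used to look for varying associations, but the text does not settle it. The point does not depend on it.

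**A reader might infer that transportability is not examined at all.** The documents do not support that. The per-database runs, the study-by-predictor interactions and the random study effect examine between-study variation in associations, and Aim 5 tests Model #1 indirectly. What they leave open is calibration in a database that played no part in development.

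**A reader might infer that the final model is badly over-fitted,** because re-fits in very small databases give inflated ROC areas. That does not follow. NOMASS and APRIS hold 60 + 83 = 143 of 3,101 patients (4.6%). A simulation at the pooled size, with 8 or 12 assumed predictors from one common population, gave an apparent area of 0.638 against 0.630 to 0.631 in new data, so optimism is about 0.01. The worry is shift between populations.

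**Raw PFO shares are not model error.** Correct. Case-mix adjustment could raise or lower the between-database variance, so the spread is no bound in either direction on miscalibration.

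**Aim 3 builds its model "using an approach otherwise similar to that described for Aim 2",** so the same gap might be read into Model #2. It is not comparable, because Model #2 has its own external validation in the medical arms.

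**Conclusion.** The point holds in this form: the article describes no out-of-sample discrimination or calibration of Model #1, its per-database check is in-sample on either reading, and the PFO-only trials cannot make up for it. The size of any miscalibration is unknown, since nothing planned would measure it in an unseen database. What can be given is the leverage: 3 points of propensity error at 0.25 is worth about 8.5 to 16 points of attributable probability over the control rates in Figure 1, and 2 to 4 points at 0.50. This rests on Aim 2's two assumptions and on the formula derived from them. The spread of 20.5% to 54.1% in raw PFO share makes a baseline shift plausible but does not prove one. Aim 4's remark that ranking by attributable probability is insensitive to the control rate does not remove the concern, because the absolute probability is combined with a second model. This is a change worth making, not a flaw that invalidates the design.

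**What to change.** Make leave-one-database-out (internal-external) validation the performance check for Model #1, over the eight databases with and without PFO. For each one, repeat the whole model building on the other seven, including predictor selection and removal of inconsistent predictors, then apply the fixed coefficients to the database left out. Report ROC area, calibration-in-the-large and calibration slope, pooled by random effects, and note that the held-out estimates from NOMASS and APRIS will be imprecise. Showing the calibration error on the attributable-probability scale as well would make its consequence visible. Finish this before the composite index is frozen under Aim 4. Keep the per-database runs as a description of coefficient consistency, and state whether they re-fit or apply the model.

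The cost is analysis code; no new data are needed. The smallest training set, 1,975, is the size the article itself treats as giving ample power. The downside is that reported performance may be lower and more variable.
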